### Who will take informed consent? {26a}

At baseline, the principal investigator (MK) will explain the purpose of the trial to the legal guardian and will obtain their written informed consent upon enrollment.

### Additional consent provisions for collection and use of participant data and biological specimens {26b}

In the written informed consent, we include additional item for getting permission for future research opportunities which participants can say no and only taking part to main study.

### Interventions

#### Explanation for the choice of comparators {6b}

Patients in the intervention and control groups will be given the standard treatments. l-carnitine and placebo (maltodextrin) will be used as adjunctive therapy. Intervention and control pill boxes will be produced by the Karen Pharma and Food Supplement Company, Iran, with similar shape, odor, taste, and package and tagged A and B. Maltodextrin was selected as placebo control because this carbohydrate is digested easily and has a similar taste and appearance as l-carnitine, and it does not interfere with the microbial ecology of the gastrointestinal tract or with gut metabolism and function.

#### Intervention description {11a}

In both groups, after hemodynamic resuscitation and stabilization, nutritional support will begin in the first 24–48 h. Nutritional support with 25 kcal/kg of energy will be determined and will be administered as a bolus method, 7 times in 24 h. Patients will receive all common medications and routine treatment and will be visited daily by a physician who will assess gastrointestinal function.

The intervention will be as capsules in the form of 1000 mg of l-carnitine that will be manufactured by Karen Pharma and Food Supplement company, Iran. Placebo capsules of identical color, odor, and taste will also be produced by above mentioned company.

We consider 3000 mg as the appropriate intervention dose because this dose has low adverse effects and studies show that supplementation > 2 gr/day might have a greater effect [18–20]. l-carnitine and placebo will be tagged A and B by Karen Pharma and Food supplement company and prescribed to the patients using a double-blind procedure. Placebo or l-carnitine will be administered orally or with enteral nutrition (enteral tube feeding) three times a day in 9:00, 15:00, and 21:00 o'clock for 7 days (patients will receive totally 3000 mg l-carnitine or placebo for 7 days).

#### Criteria for discontinuing or modifying allocated interventions {11b}

Though a limited adverse impact has been reported [21], if there are any adverse reactions to the intervention, the intervention will be discontinued and reported to the Isfahan University of Medical Sciences Ethics Committee for a decision. If any participants or their legal guardians ask to cease interventions, we will finish those.

#### Strategies to improve adherence to interventions {11c}

MK will implement the trial and prescribe drugs orally or via enteral tube feeding and another investigator (BA) ask him to return the pill box daily and will check the number of capsules into the pill box. At the end of the study, if the patients received less than 80% of capsules, he/she will be excluded from the study.

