### Eligibility criteria {10}

Inclusion criteria:Septic patients who will be hospitalized in the ICU. Sepsis will be diagnosed using new definitions for sepsis and septic shock (Sepsis-3) by Surviving Sepsis Campaign International Guidelines for Management of Sepsis and Septic Shock: 2016 [17]. Septic patients will be recruited < 24 h after diagnosisAge between 20 and 65 yearsLegal guardian writes informed consentExclusion criteria:Patients who stay in hospital for < 3 daysPatients who receive parenteral nutritional supportPatients who receive enteral or oral nutrition at first but then transfer to parenteral nutrition due to the contraindicationsPatients who will not be able to receive enteral nutrition or those who will not be able to receive enteral nutrition in the future because of incomplete resuscitation and hemodynamic instability or gastrointestinal disorders including nausea, persistent vomiting, ileus, intestinal obstruction, uncontrolled diarrhea (> 500 ml/day), high-output fistula (> 500 ml/day), and intestinal inaccessibilityPatients with cancer undergoing chemotherapy and use cisplatin and other drugs that have interaction with l-carnitine; phenobarbital and phenytoin, pivalic acid, valproic acid and ifosfamide, and levetiracetamPatients undergoing dialysis, severe and progressive septic shock or sepsis, infection processes, DIC (diffuse intravascular coagulation), and any inflammatory interactions that interfere with the intervention process will be excludedPregnancyPatients with BMI < 18.5 kg/m^2^Patients who require frequent blood transfusionsAny unwanted side effects in patients after taking a supplement or placebo

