#### Methods in analysis to handle protocol non-adherence and any statistical methods to handle missing data {20c}

Intention-to-treat analysis will be carried out for missing data. Patient exclusion reasons will be reported completely. We plan to perform sensitivity analyses to explore the effect of departures from the missing data assumptions made in the efficacy analyses. Multiple imputation will be used for missing data.

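### Rules that exclude patients for events arising after randomisation contradict the intention-to-treat analysis that the protocol names, and can distort mortality and bias the comparison

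*Protocol article*

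**What the plan says.** Four rules remove patients for events that belong wholly or largely to the period after randomisation.

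- Strategies to improve adherence {11c}: when the study ends, "if the patients received less than 80% of capsules, he/she will be excluded from the study".
- Eligibility criteria {10}: any unwanted side effect after taking supplement or placebo is an exclusion criterion.
- Eligibility criteria {10}: "Patients who stay in hospital for" less than 3 days are excluded.
- Eligibility criteria {10}: patients who start on enteral or oral feeding and are later moved to parenteral nutrition are excluded.

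The same eligibility section recruits patients less than 24 h after diagnosis. It also lists "severe and progressive septic shock or sepsis, infection processes" among the exclusions, without saying when this is assessed.

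On the analysis, section {20c}, whose heading covers both non-adherence and missing data, says: "Intention-to-treat analysis will be carried out for missing data". It adds "Patient exclusion reasons will be reported completely" and "Multiple imputation will be used for missing data", and plans sensitivity analyses. On adverse reactions, section {11b} says only that "the intervention will be discontinued and reported to the Isfahan University of Medical Sciences Ethics Committee for a decision"; it does not say that the patient leaves the study.

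**The concern.** An intention-to-treat analysis keeps every randomised patient in the assigned arm. A rule that excludes a patient from the study for too few capsules, a side effect, a short stay or a change of feeding route does the opposite. Each of these events can depend on the course of the illness, and some can depend on the treatment. An analyst holding this protocol could defend either population, and could choose between them after the data are known.

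Two things are at stake. The first is 28-day mortality, a secondary outcome. Patients who die early cannot take enough capsules, so the rule tends to remove deaths. The second is the treatment comparison, for mortality and for the primary biomarkers. If removals differ by arm, the retained groups are no longer the randomised groups. The protocol's adverse-event section {22} itself names diarrhoea and fish odour as possible effects of l-carnitine, so unequal removal for side effects is foreseeable.

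**Working it through.** **Which rules can be applied before randomisation?** The capsule count cannot, because it is taken at the end of the study. The side-effect rule cannot, because it requires that study product has been taken. Transfer to parenteral nutrition after a start on enteral or oral feeding is, with recruitment inside 24 h of diagnosis, largely a later event. So is a stay under 3 days, except for patients already in hospital for some days before sepsis was diagnosed.

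**Does another section keep excluded patients in the analysis?** Section {20c} attaches intention-to-treat to missing data and says that exclusion reasons are reported. It does not say that excluded patients are followed or analysed as randomised. The section on retention and complete follow-up {18b} is marked not applicable. The sample size section {14} raises 24 per group to 30 for drop-outs, which is consistent with analysing only those retained.

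**The protocol's sample size figure.** n = 2 × (1.96 + 0.84)² × 37² / 30² = 23.85, so 24 per group; this reproduces. Going from 24 to 30 implies a 20% allowance (1 − 24/30). By the normal approximation at the same inputs, power is 72.7% with 20 per group, 80.2% with 24 and 88.1% with 30. The figure for 30 assumes that the effect is not diluted by non-adherence.

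**What the 80% rule means.** Doses are given "three times a day in 9:00, 15:00, and 21:00 o'clock for 7 days", one 1000 mg capsule each, 3000 mg a day.

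- Planned capsules: 3 × 7 = 21.
- Threshold: 0.80 × 21 = 16.8, so 17 are needed (17/21 = 81.0%; 16/21 = 76.2%).
- By the end of day 5: 5 × 3 = 15. The 16th is the first dose of day 6 and the 17th is the second.

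This takes 21 as the denominator and a full first day of dosing. On that reading, anyone who dies or stops before the second dose of day 6 is excluded.

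**Illustration for absolute mortality.** The background section {6a} gives 28.3% and 41% for severe sepsis. Let m be true mortality and f the share of deaths before the 17th capsule. The values of f, 0.25 and 0.50, are assumptions. If only those deaths are removed, apparent mortality = m(1 − f) / (1 − mf).

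| m | f | Deaths lost of 30 per arm | Apparent mortality |
|---|---|---|---|
| 28.3% | 0.25 | 2.1 | 0.2123/0.9293 = 22.8% |
| 28.3% | 0.50 | 4.2 | 0.1415/0.8585 = 16.5% |
| 41% | 0.25 | 3.1 | 0.3075/0.8975 = 34.3% |
| 41% | 0.50 | 6.15 | 0.2050/0.7950 = 25.8% |

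**If early-discharged survivors are removed too.** With 20% of survivors also leaving (assumed), apparent mortality = m(1 − f) / [m(1 − f) + 0.8(1 − m)]:

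- m = 28.3%: 0.2123/0.7859 = 27.0% (f = 0.25) and 0.1415/0.7151 = 19.8% (f = 0.50).
- m = 41%: 0.3075/0.7795 = 39.4% (f = 0.25) and 0.2050/0.6770 = 30.3% (f = 0.50).

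The distortion shrinks, and it depends on a discharge share that the document does not give.

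**The case against.** The best defence is section {20c}. Its heading includes non-adherence, and it names intention-to-treat, multiple imputation and sensitivity analyses. Exclusion could mean that treatment stops and missing outcomes are imputed. No sentence says so, but none says that mortality is computed in retained patients only. The consequences must therefore be stated as what can happen. The contradiction in the wording stands.

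A reader might infer four stronger things that the document does not support.

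- *That side effects vanish from the safety data.* Section {22} has all adverse events reported, {11b} sends adverse reactions to the ethics committee and {21b} plans an interim safety analysis. What can be lost is the affected patients' place in the comparison between arms.
- *That the septic shock item lets the investigator remove anyone who worsens.* It may be a screening state, and the list ends by limiting itself to conditions that interfere with the intervention. It is ambiguous and needs clarifying; it is not shown to be a removal rule.
- *That a false mortality benefit of a given size follows.* Removing 10% to 20% of the active arm and nobody on placebo, at 1.5 to 2 times average mortality, yields 1.6 to 10.3 points with no true effect. But the rule covers both arms, the trial is blinded, and the only side effects named are described as minor. Nothing in the document supports those inputs.
- *That the mortality figures above show bias between arms.* They describe absolute mortality. Equal removal in both arms mainly distorts that and narrows the population studied.

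It is also fair to say that {11c} does not define the denominator of its 80%, and that the document does not say whether dosing continues after discharge.

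**Conclusion.** The point holds as a contradiction in the text. The exclusions in {10} and {11c} cannot be followed together with the intention-to-treat analysis in {20c}, and the side-effect exclusion in {10} also conflicts with {11b}, which only discontinues the intervention. This is not a detail left to an analysis plan, because the protocol states the exclusions outright.

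The size of any bias cannot be known from the document. The mortality ranges rest on the 21-capsule denominator, on the assumed 25% to 50% of deaths before the 17th capsule and on the removal of deaths only. A bias in the treatment comparison requires that removals differ by arm, which is plausible for side effects but not established. No size can be given for the biomarkers. The matter should be settled before recruitment, because outcomes not collected on excluded patients may not be recoverable.

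**What to change.** Reconcile sections {10}, {11b}, {11c} and {20c}:

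1. In {10}, keep only conditions that can be assessed before randomisation, and say whether the septic shock or sepsis item is a screening state.
2. List low capsule intake, side effects, stay under 3 days and later transfer to parenteral nutrition as post-randomisation events, after which the patient stays in follow-up to day 28.
3. In {20c}, state that mortality, hospital stay and the primary biomarkers are analysed in all randomised patients by assigned arm, with the imputation and sensitivity analyses already named. Say explicitly how biomarkers missing because of death are handled, since such patients have no end-of-trial sample under any rule.
4. Report safety in all patients who took any study product.
5. Keep patients with at least 80% of capsules only as a labelled per-protocol sensitivity analysis, and define the denominator of the 80%.

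The cost is wording, some extra follow-up records, the effort of obtaining end-of-trial samples from patients discharged early, and possible dilution of the effect by non-adherence. No larger sample is needed at the protocol's own inputs unless that dilution is material. Nothing here proposes a clinical rule for stopping treatment.

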#### Relevant concomitant care permitted or prohibited during the trial {11d}

Supplementation with placebo or l-carnitine will not require alteration to usual care pathways (including use of any medications). ‍On the other hand, supplementation with placebo or l-carnitine will not require alteration to usual care pathways (including use of any medications).

#### Treatment strategies

Controlling source: After sample culture drainage, the clinician prescribes antibiotics (broad-spectrum), antiviral, and or antifungal agents especially in immunodeficiency patient. Then, antimicrobial agents will be limited according to the result of the culture for controlling the source of the infection [9]Fluid therapy: For ameliorating hypotension and decreased mean arterial pressure (MAP), the Surviving Sepsis Campaign (SSC) recommended that 30 mg/kg fluid should be administered initially [2]Target blood pressure: Low MAP is related to more mortality rate and kidney injury; therefore, for MAP < 65 mmHg vasopressor therapy should be initiated [8]Other supportive agents: Many auxiliary agents have been researched such as nutritional antioxidants (vitamin C and vitamin B_1_ [9], glutamine, arginine, and selenium [17]), corticosteroids, and immunoglobulins [2]

#### Provisions for post-trial care {30}

Although no risk of harm will consider for our intervention, the patients will be followed for 1 week after intervention.

#### Outcomes {12}

All assessors in this trial will be blinded to intervention allocation.

Serum CRP and ESR as an inflammatory agent, serum lactate dehydrogenase (LDH) as a marker of cell injury, total oxidative stress (TOS), and total antioxidant capacity (TAC) as an oxidative stress biomarker will be measured as our primary outcomes. Secondary outcomes include evaluating duration of hospitalization (days) and 28-day mortality rate, differences in albumin (Alb), alanine aminotransferase (ALT), aspartate aminotransferase (AST), blood urea nitrogen (BUN), and creatinine in blood. Anthropometric variables such as weight, height, body mass index (BMI), mid arm circumference (MAC), and calf circumference will be appraised at baseline.

Estimation of patient height: Due to the limitations in the ICU, the patients’ height is calculated based on the following formula [22]:
$$ \mathrm{Height}\ \left(\mathrm{cm}\right)=153.492-\left(7.97\times \mathrm{sex}\ \left[\mathrm{sex}:\mathrm{man}=1,\mathrm{woman}=2\right]\right)+\left(0.974\times \mathrm{ulna}\ \mathrm{length}\ \left[\mathrm{in}\ \mathrm{cm}\right]\right) $$

Estimation of patient weight: Due to the limitations in the ICU, the patients’ weight is calculated based on Chumlea I formula [23]:
$$ \mathrm{Men}:\left(\mathrm{MAC}\times 2.31\right)+\left(\mathrm{calf}\ \mathrm{circumference}\times 1.50\right)-50.10 $$$$ \mathrm{Women}:\left(\mathrm{MAC}\times 1.63\right)+\left(\mathrm{calf}\ \mathrm{circumference}\times 1.43\right)-37.46 $$

Blood drawing will be executed at baseline and end of the trial. About 10 ml volume of fasted blood (at 6:00 o’clock before first meal) will be collected and then centrifuged, with the serum separated from the sediment, and preserved at temperature of − 20 °C.

Calf circumference method of measurement: The circumference of the leg muscle is measured so that the patient is in the supine position. The patient’s left knee rises high enough to form a right corner between the thigh and the leg. We place the tape around the leg muscle and move it along the leg muscle to meter the largest circumference without any pressure to the subcutaneous tissue [24].

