### Sample size {14}

The number of samples considering the type I error *α* = 0.05 and the type II error *β* = 0.20 with 80% test power and standardized effect size equal to *Δ* = 30 of the following formula based on to detect the inflammation effect based on changes in CRP (as the main outcome of this study) by l-carnitine supplementation (control group: 99.96 ± 33.16, intervention group: 98.48 ± 37.01) using the findings of Noormandi et al. CRP index (mg/dl) [25]:
$$ n=\frac{2\left[{\left({Z}_{1-\frac{\alpha }{2}}+{Z}_{1-\beta}\right)}^2\times {S}^2\right]}{\varDelta^2}=\frac{2\left[{\left(1.96+0.84\right)}^2\times {(37)}^2\right]}{30^2}=23.85 $$

The required sample size in each group has been equal to 24 people, and with considering the drop out patients, the sample size will be practically 30 patients in every group, which we will consider a total of 60. It seems that this sample size is small; however, several articles which conducted among ICU patients used a small sample size based on a formula like our ones and worked on about 60 patients [26–28].

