### Statistical methods

#### Statistical methods for primary and secondary outcomes {20a}

Analyzing data will be performed in the SPSS 16 (version) software. Normality will be checked by Kolmogorov-Smirnov test. Qualitative data will be reported as frequencies, normal continuous quantitative as mean (± SD) and median (IQR) for others.

Differences within group will be assessed with paired *t*-test and Wilcoxon rank-sum test.

Between group differences also will be assessed using independent *t*-test and Mann-Whitney *U* test. The significance level will be considered *p* < 0.05.

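### Five biomarkers are named as primary, but the sample size treats CRP alone as the main outcome; if any one of the five could carry the trial, the false-positive chance is up to 22.6% rather than 5%.

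*Protocol article*

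**What the plan says.** Three sections of the protocol article bear on this.

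- **Outcomes {12}** gives one list of primary outcomes, with no ranking. It opens with "Serum CRP and ESR as an inflammatory agent, serum lactate dehydrogenase (LDH) as a marker of cell injury" and closes with "total oxidative stress (TOS), and total antioxidant capacity (TAC) as an oxidative stress biomarker will be measured as our primary outcomes". That makes five.
- **Sample size {14}** says the calculation is "based on changes in CRP (as the main outcome of this study) by l-carnitine supplementation". Its error rates are "type I error *α* = 0.05 and the type II error *β* = 0.20 with 80% test power". No other marker enters the calculation.
- **Statistical methods for primary and secondary outcomes {20a}** says "Between group differences also will be assessed using independent *t*-test and Mann-Whitney *U* test", followed by "The significance level will be considered *p* < 0.05". The same threshold serves primary and secondary outcomes alike.

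The article states no testing order, no alpha split, no requirement that all five succeed, and no rule that CRP alone decides.

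**The concern.** One section names five primary outcomes and another names one main outcome. A reader of the results could not tell from the protocol which finding confirms the hypothesis. The Objectives {7} section covers inflammation and oxidative stress together, and says a confirmed hypothesis may lead to l-carnitine being used alongside existing therapies, so the meaning of a confirmed result matters.

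Two things are at stake. First, if any of the five can carry the claim, the 5% error rate in the sample size describes the CRP comparison only, not the trial's overall conclusion. Second, the marker that carries the claim could be chosen after the results are known.

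**Working it through.** **Inputs from the protocol**

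- Number of primary outcomes: k = 5 (Outcomes {12}).
- Threshold for each test: 0.05 ({20a}); two-sided, since the sample size formula uses 1.96 for 1 − α/2.
- CRP difference 30, SD 37, 80% power, 24 per group before dropout and 30 per group after (Sample size {14}).

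**Not in the protocol, so assumed:** the correlations among the five markers. I use one common correlation, r, and vary it.

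**Step 1. Reproduce the stated sample size.**

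n = 2 × (1.96 + 0.84)² × 37² / 30² = 2 × 7.84 × 1369 / 900 = 23.85, rounded up to 24 per group. This matches the protocol. For CRP as the only primary outcome, the calculation does what it says.

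**Step 2. False-positive chance if any one of five tests suffices.**

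For independent tests: 1 − 0.95⁵ = 1 − 0.7738 = 0.226.

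For correlated tests: 1 − P(all five |Z| ≤ 1.96) under a multivariate normal with common correlation r, by numerical integration.

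| Common correlation r (assumed) | Chance of at least one false positive |
|---|---|
| 0 | 22.6% |
| 0.3 | 20.9% |
| 0.5 | 18.3% |
| 0.7 | 14.8% |
| 0.8 | 12.7% |
| 0.9 | 10.2% |

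Simulated two-sample t-tests agree. At r = 0 they give 22.5% with 24 per group and 22.6% with 30. At r = 0.7 they give 15.0% and 15.2%.

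**Step 3. The same quantity under other decision rules.**

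- CRP alone decides: 5%.
- All five must be significant: at most 5%.

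**Step 4. Power for CRP if five primary outcomes are kept with Bonferroni control (0.05 / 5 = 0.01 each).**

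The standardized difference is 30 / 37 = 0.811. Power by noncentral t:

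| Per group | Alpha 0.05 | Alpha 0.01 |
|---|---|---|
| 24 (full dropout allowance used) | 78.5% | 55.2% |
| 30 (no dropout) | 87.0% | 68.2% |

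The normal approximation behind the protocol's formula gives slightly higher values at alpha 0.01: 59% and 71%.

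Size needed for 80% power at alpha 0.01 by the protocol's own formula: 2 × (2.576 + 0.84)² × 37² / 30² = 35.5, so 36 per group before dropout. By noncentral t it is 38.

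**The case against.** The strongest reply is that the protocol never says one significant marker out of five is enough. A reader might infer from the list and the single threshold that the trial's false-positive rate simply is 15% to 23%. The document does not support that. The rate depends on a decision rule that the protocol neither states nor excludes, and if the sample size section governs, the rate is 5%. Nor is 15% a floor: it corresponds to an assumed correlation of 0.7, and higher correlations give lower figures. A single common correlation across the five markers is itself an assumption. All of this stands, and the error rate is given here only as a conditional figure.

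A second reply is that a condensed protocol article may leave multiplicity to an analysis plan that is not shown. That is fair for the choice of adjustment method, and the missing method is not the point. Such a plan would still leave two sections of this document disagreeing on how many primary outcomes there are.

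A third reply is that sizing a trial on one key outcome while listing others is common, and that the 5% does hold for CRP. Both are true. The defect is that the other four are given the same primary status as CRP.

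The abstract does not mention LDH among the markers. A reader might take that as a third, conflicting list, but the abstract ranks no outcome as primary, so it is not evidence of conflict.

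**Conclusion.** The conflict between Outcomes {12} and Sample size {14} is real and lies wholly within the document. If any one of the five markers can count as a positive primary result at 0.05, the false-positive chance is up to 22.6%. Even at an assumed common correlation of 0.9 it is about 10%, twice the nominal rate. If CRP alone decides, it is 5% and the list of primary outcomes is wrong. On either reading one of the two sections has to change, and this should be done before results are known. The sample size arithmetic is correct for CRP as sole primary outcome; it does not provide 80% power for CRP if alpha is split equally across five.

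**What to change.** In Outcomes {12}, name CRP as the single primary outcome, in line with Sample size {14}. Move ESR, LDH, TOS and TAC to secondary, either Holm-adjusted as a family or labelled exploratory. In {20a}, state that the trial's conclusion rests on the between-group comparison of CRP at two-sided 0.05. Bring the registry entry into line where it differs.

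The cost is wording. There are no extra patients, assays or visits, no loss of power for CRP, and all five markers are still measured and reported. The real downside is scientific: four markers lose primary status, including both oxidative-stress markers, although oxidative stress is among the stated objectives.

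If the investigators prefer to keep five primary outcomes with familywise control, that is a valid alternative. They would then need to state the procedure and restate the power. With Bonferroni at 0.01, power for CRP is about 55% at 24 per group and 68% at 30, and 80% would need about 36 per group by the protocol's formula (38 by noncentral t) before dropout.

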**Method and design:**

In this double-blind, randomized controlled clinical trial, we will use block randomization of 60 patients with sepsis, aged between 20 and 65 years from Al-Zahra Hospital, Isfahan, Iran. The intervention group (*n* = 30) will receive three capsules of l-carnitine (each capsule contains 1000 mg l-carnitine; totally 3000 mg/day) for 7 days, and a control group (*n* = 30) will receive a placebo with the same dose and for the same duration in addition to usual care. At baseline, scores for clinical and nutritional status (Acute Physiology and Chronic Health Evaluation II (APACHE II), Sequential Organ Failure Assessment (SOFA), Quick SOFA (qSOFA), and NUTRIC Score) will be assessed. At beginning and end point of the study, inflammatory markers (CRP, erythrocyte sedimentation rate (ESR)), oxidative stress status (total oxidative stress (TOS), total antioxidant capacity (TAC)), and clinical variables will be evaluated also. The mortality rate will be assessed within 28 days of the beginning of the intervention.

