#### Plans to promote participant retention and complete follow-up {18b}

Not applicable.

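### Hospital stay is a raw day count with no provision for death, so the arm with more deaths can look better; the exclusion, imputation and follow-up statements also leave deaths unsettled

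*Protocol article*

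**What the plan says.** All references are to the Protocol article.

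- **Outcomes {12}:** "Secondary outcomes include evaluating duration of hospitalization (days) and 28-day mortality rate". The primary outcomes are blood markers (CRP, ESR, LDH, TOS, TAC), and "Blood drawing will be executed at baseline and end of the trial".
- **Statistical methods {20a}:** groups are compared by the independent t-test or Mann-Whitney test. This is a general paragraph that does not name hospital stay, but no other between-group method is given for it and death is not mentioned.
- **Eligibility criteria {10}:** a hospital stay under 3 days is an exclusion. **Strategies to improve adherence {11c}:** a patient found at the end to have received under 80% of the capsules is excluded.
- **Methods for non-adherence and missing data {20c}:** an intention-to-treat analysis, sensitivity analyses on the missing-data assumptions, and "Multiple imputation will be used for missing data".
- **Abstract, Method and design:** "The mortality rate will be assessed within 28 days of the beginning of the intervention".
- **Provisions for post-trial care {30}:** "the patients will be followed for 1 week after intervention". The item on retention and complete follow-up {18b} is answered "Not applicable".

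**The concern.** Death and hospital stay compete: a patient who dies in hospital has a stay cut short by the worst possible result. If the raw count is compared between arms, excess deaths pull the mean and the ranks in the direction that looks like benefit. The trial hopes to change mortality (Objectives {7}, Discussion), so unequal deaths between arms are a case that it must be ready for.

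Three related statements add to the problem. The two exclusions act after treatment has started and would remove early deaths, while the missing-data section promises intention-to-treat. The imputation sentence, taken literally, supplies end-of-trial biomarker values for patients who were dead when the sample was due, and those biomarkers are the primary outcomes. Finally, no passage says how vital status at day 28 is obtained for a patient who has already been discharged.

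**Working it through.** The plan gives no expected stay, no timing of deaths and no mortality for its own population, so there is no plan figure on this point to reproduce. The size is an illustration under assumptions.

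**Inputs**
- From the documents: three doses a day for 7 days, taken as one capsule each, so 21 capsules (Intervention description {11a}; Abstract); the 80% rule {11c}; 41% and 28.3% mortality, quoted in Background {6a} for severe sepsis in Europe and the USA and used here only as two example arm rates.
- Assumed: every survivor stays 18 days and meets the capsule rule; deaths are uniform over days 1 to 14 (mean day 7.5).

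**1. All randomised patients kept**
- Mean stay = m × 7.5 + (1 − m) × 18.
- m = 0.41: 3.075 + 10.62 = 13.70 days.
- m = 0.283: 2.12 + 12.91 = 15.03 days.
- Difference = (0.41 − 0.283) × (7.5 − 18) = −1.33 days. The arm with more deaths looks better. Every death also ranks below every survivor, so Mann-Whitney moves the same way.
- Other assumptions: with deaths at day 5 to 10 and survivors staying 15 to 20 days, the false benefit runs from 0.127 × (15 − 10) = 0.6 to 0.127 × (20 − 5) = 1.9 days.

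**2. Early deaths removed by the 80% rule**
- 0.80 × 21 = 16.8, so 17 capsules are needed. Five full days give 15, and the 17th falls on day 6. A patient who dies on day 4 has had at most 12 (57%) and is excluded.
- Deaths on days 1 to 5 removed (9/14 remain, mean day 10): death shares 0.2636/0.8536 = 30.9% and 0.1819/0.8989 = 20.2%. Difference = (0.3088 − 0.2024) × (10 − 18) = −0.85 days.
- Deaths on days 1 to 6 removed (8/14 remain, mean day 10.5): shares 0.2343/0.8243 = 28.4% and 0.1617/0.8787 = 18.4%. Difference = (0.2842 − 0.1840) × (10.5 − 18) = −0.75 days.
- The same removal changes mortality itself: 41% against 28.3% (12.7 points) would be reported as 30.9% against 20.2% (about 10.6 points) or 28.4% against 18.4% (10.0 points).

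**3. Hospital-free days to day 28, death = 0, all patients kept**
- A survivor scores 28 − 18 = 10. Means: 0.59 × 10 = 5.90 and 0.717 × 10 = 7.17.
- The arm with more deaths is now 1.27 days worse, so the sign is right.

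**4. Follow-up**
- 7 treatment days + 7 days = about day 14, against day 28 for mortality: 14 days without a described contact.

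**The case against.** Several points on the other side have force.

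- A reader might infer that the plan scores an early death, say on day 4, as a short and favourable stay. The documents do not say so. Such a patient falls under the capsule rule, and a death before day 3 also falls under the stay exclusion. This stands, and it is why the smaller figures are shown. It does not clear the plan: intention-to-treat would keep the same patients, and later deaths shorten the stay under either reading.
- A reader might infer that follow-up ends at day 14. It is not shown to. The one-week statement sits under post-trial care, the Abstract sets a 28-day mortality assessment, and the answer under {18b} concerns retention measures; it does not say that vital status goes uncollected. What stands is that these statements have not been reconciled.
- A reader might take 28.3% to 41% as this trial's mortality. Those are severe-sepsis rates, and the trial excludes several high-risk groups, including severe and progressive septic shock or sepsis. Both the level and the 12.7-point gap are illustrative.
- The imputation sentence does not mention death, and its details may sit in an analysis plan that is not shown. Sensitivity analyses are promised, but as described they concern departures from missing-data assumptions, which is a different matter from a value that does not exist.
- Mortality is reported beside stay, so a reader could notice excess deaths. With 30 patients per arm that is a weak safeguard, and it fails if the exclusions remove deaths from both outcomes.
- A biomarker comparison among survivors is itself open to selection. This stands, and the fix allows for it.

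**Conclusion.** The point holds in a limited form. Raw hospital days with a t-test or Mann-Whitney and no provision for death can favour the arm with more deaths. Under the stated assumptions the false benefit is about 1.3 days with all randomised patients kept, and about 0.75 to 0.85 days if the capsule rule removes deaths before about day 6 or 7. The direction needs only that patients who die leave the count earlier than survivors do. The size depends on assumed stay, assumed timing of deaths and borrowed mortality rates.

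The two exclusions contradict intention-to-treat and would also understate 28-day mortality. Read literally, the imputation rule covers patients who died before the draw. The follow-up statements need reconciling; they do not prove that observation stops at day 14. Hospital stay is a secondary outcome, so that part does not bear on the CRP comparison, whereas the imputation part does affect the primary biomarkers.

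**What to change.** - **Stay:** analyse hospital-free days to day 28, with death scored 0, in all randomised patients, in place of raw hospital days. Report stay in survivors descriptively. Other death-adjusted endpoints would also serve; this one uses data already collected.
- **Analysis set:** reconcile {10} and {11c} with {20c}, so that every randomised patient counts in 28-day mortality and in the stay outcome.
- **Biomarkers:** do not impute values after death. Label the comparison as one among patients alive at the end-of-trial draw, and add a sensitivity analysis that ranks earlier deaths worst, because the survivor comparison is open to selection.
- **Follow-up:** reconcile {30} and {18b} with the Abstract and {12} by stating a day-28 vital-status check, by record review or telephone, for every randomised patient, counted from the start of the intervention as the Abstract has it.

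Cost: a less familiar endpoint that scores a death the same as a patient still in hospital at day 28, one extra analysis, and one call or record check per discharged patient.
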